### Data handling

Every patient included in the study will be assigned a unique identification number created by means of an algorithm based on the health centre, the patient’s initials, and the patient’s date of birth.

The DCBs will be developed using Teleform Desktop v9.1 format, an automated questionnaire reading programme. Teleform contains a verification model that guarantees the quality of data entry. Two security copies of all the data entered will be made every month and stored on a magnetic tape (IBM 3500 backup 400 Gb server).

### Statistical analysis

The statistical analyses will be carried out using the SPSS programme for Windows v 12.

Descriptive, labelled analyses and data refinement: evaluation of the atypical and extreme values (“outliers”), detection and labelling of the lost and/or not applicable values. We will perform descriptive analysis, with continuous variables summarised by their means and standard deviations for normal distributions, and by median and 25th and 75th percentiles for non-normal distributions.

Basal comparative analysis: Comparison of socio-demographic characteristics, smoking behaviour and other variables collected by means of the t Student and chi-squared tests. If normality is not met, non-parametric tests will be applied.

Final comparative analysis: Comparison of the dependent variables in both groups by means of the t Student and the chi-squared tests. If normality is not met, non-parametric tests will be applied. The relevance of the intervention will be determined from the percentage of patients with sustained smoking cessation in both groups - the relative risk (RR), the reduction in relative risk (RRR), the reduction in absolute risk (RAR), and the number of intent to treat patients (ITT) necessary will be calculated. All the analyses will be carried out based on intent to treat. The patients lost to follow-up will be considered as smokers. The level of statistical significance is established at 5% (bilateral).

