### Sample size

Accepting an alpha risk of 0.05 and a beta risk of 0.20 in a bilateral contrast, and estimating a rate of loss to follow-up of 10%, 471 subjects in both the control group (CG) and the intervention group (IG) are required in order to detect a difference equal or superior to 5% between groups. A proportion of 5% smoking cessation is estimated in the CG. In total, a sample size of 942 subjects is required.

Forty-eight health care professionals from 16 health care centres will participate in the study. It is expected that each professional will include approximately 20 subjects to attain the sample size required.

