### Random allocation to study arms

The randomised scheme will be carried out in blocks of 20, using a computer program. The allocation of each patient will be determined using a table of randomised numbers, and this number will be indicated on a report placed in closed, opaque envelopes sequentially numbered. Each professional will have 20 envelopes, one for each subject. The professional will not know the randomisation scheme. The socio-demographic variables, together with those on the smoking habits of the participants that decline to participate in the study, will be collected in a separate report. The inclusion period for subjects will be 12 months.

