#### Independent measures

Type of intervention: brief advice or brief advice together with CO-oximetry. At baseline, the following information will be obtained: (a) socio-demographic variables: gender, age, social class measured by means of two indicators suggested by the Spanish Society of Epidemiology: educational level and occupation; (b) regarding the patient’s smoking behaviour: number of cigarettes/day and number of years the patient has been smoking (the number of packets/year will be calculated based on this information); concentration of nicotine and tar smoked currently (obtained from the type of tobacco consumed); number of times the patient has tried to quit smoking and reasons for relapse; maximum amount of time without smoking; tobacco consumption during work, with family and/or friends; physical dependency on nicotine using a simplified version of the Fagerström test; phase of the smoking cessation process: Prochaska and DiClemente phases (pre-contemplation, contemplation, preparation, cessation and relapse); any intervention to quit smoking during the past year; (c) other measures: consumption of other legal drugs (alcohol, psychopharmacological drugs); consumption of illegal drugs (cannabis, cocaine and others); basal disease associated with tobacco consumption (Chronic Obstructive Lung Disease, cancer, ischemic myocardiopathy, cerebrovascular disease); other cardiovascular risk factors (HTA, diabetes mellitus, dyslipidaemia, obesity); mental illness.

At months 6 and 12 the following data will be collected: Smoking behaviour/status (does the patient smoke or has he/she quit); date of smoking cessation, whether the patient has quit smoking; time interval without smoking between date of intervention till six month assessment; participation in a programme for smoking cessation since the beginning of the study.

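### Allocation is in effect blocked by professional, but the final tests ignore professional and the recorded baseline values: a small loss of efficiency, not a validity error

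*Protocol article*

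**What the plan says.** Random allocation to study arms states that "The randomised scheme will be carried out in blocks of 20, using a computer program", and that "Each professional will have 20 envelopes, one for each subject". Sample size expects 48 professionals to include about 20 subjects each. Intervention has the including professional deliver whichever arm is assigned, so every professional treats subjects in both groups.

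Independent measures lists the baseline data. They include "number of cigarettes/day and number of years the patient has been smoking", a nicotine dependence score and the phase of change.

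Statistical analysis then sets the final comparison: "Comparison of the dependent variables in both groups by means of the t Student and the chi-squared tests". Non-parametric tests replace these if normality fails. The primary result is summarised by relative and absolute risk measures, losses count as smokers, and significance is two-sided at 5%. No term for professional, centre or any baseline variable appears.

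**The concern.** When allocation is balanced within a unit and outcomes differ between units, those differences cancel out of the treatment comparison. A test that pools everyone still counts them as noise. The design has then paid for precision that the analysis does not collect.

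Baseline variables raise a related but separate matter. Leaving them out does not bias a randomised comparison or mis-size its test, but it gives up precision if they predict outcome. This is plainest for cigarette consumption, where the baseline count of the same quantity is on file and the plan still names a t test. The switch to a non-parametric test when normality fails also lets the data decide what is estimated.

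At stake is a modest amount of power in a trial with little to spare.

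**Working it through.** **1. Inputs from the article (Sample size).** "Accepting an alpha risk of 0.05 and a beta risk of 0.20 in a bilateral contrast"; "A proportion of 5% smoking cessation is estimated in the CG"; "in order to detect a difference equal or superior to 5% between groups"; 10% loss; 471 per group. The ICC and the share of outcome variance explained by baseline variables (R²) are not given. They are assumptions below.

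**2. The plan's own figure.** Arcsine formula: h = 2[asin(√0.10) − asin(√0.05)] = 0.1925, and n = 2(1.960 + 0.842)²/h² = 423.7. Dividing by 0.9 gives 470.8, so 471 is reproduced.

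**3. Margin.** Normal-approximation power at 471 per group for 5% v 10% is 83.1%. If the 10% lost count as smokers, the rates become 0.9 × 5% = 4.5% and 0.9 × 10% = 9%, and power is 78.7%.

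**4. Blocking.** 48 × 20 = 960, against 942 needed. A block of 20 and a set of 20 envelopes per professional imply one balanced block, 10 per arm, for each professional. This is an inference; the article does not say it.

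**5. Ignoring professional, full blocks.** Simulation of 48 professionals, 10 per arm each, 20,000 trials per setting. Control rates are beta-distributed with mean 5%. The odds ratio is constant at (0.10/0.90)/(0.05/0.95) = 2.11. The stratified test uses z = Σ(a − k/2)/√Σ[100k(20 − k)/(400 × 19)], where a is the intervention-group quitters and k all quitters for a professional. The between-professional SD is √(ICC × 0.05 × 0.95).

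| Assumed ICC | SD of rates | Crude power | Stratified power | Difference | Crude type I error |
|---|---|---|---|---|---|
| 0.01 | 2.2 points | 83.6% | 83.8% | 0.2 | 4.6–4.9% |
| 0.05 | 4.9 points | 79.0% | 80.9% | 1.9 | 4.2–4.6% |
| 0.10 | 6.9 points | 72.6% | 76.9% | 4.3 | about 4% |

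The type I column spans repeat runs. Repeat runs gave power differences of 1.5 to 1.9 points at ICC 0.05 and 3.7 to 4.3 at 0.10. The stratified test held about 5% type I error.

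A second model (normal effects on the logit scale, marginal rates held at 5% and 10%, 4,000 trials) gave crude v stratified power of 83.4 v 83.8% at ICC 0.013, 84.9 v 86.4% at 0.058 and 85.3 v 89.0% at 0.136. Under the null, the crude standard error was 0.6%, 4.6% and 8.1% too wide.

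**6. Incomplete blocks (assumed recruitment).** With 8 to 20 subjects per professional, the stratified test still gained at ICC 0.05 (63.4 to 65.0%) and 0.10 (56.2 to 60.5%). At 0.01 to 0.02 the gain was nil or slightly negative. With 4 to 20 subjects, crude type I error was 4.7% at ICC 0.05 and 4.4% at 0.10, so the conservatism fades.

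**7. Ignoring baseline variables.** With one covariate and no professional effect, the crude test kept a type I error of 4.9 to 5.0% and a standard-error ratio of 1.00. Adjustment raised power by nothing at R² 0.013, from 84.3 to 86.7% at 0.058, and from 84.8 to 89.8% at 0.136. By formula, replacing n with n/(1 − R²) at R² = 0.05 lifts the 78.7% of step 3 to 80.7%.

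**8. Cigarettes per day.** With equal variances at baseline and follow-up and correlation ρ, a change score has variance 2(1 − ρ)σ² and analysis of covariance (1 − ρ²)σ². The ratio is (1 + ρ)/2. At assumed ρ of 0.3, 0.5 and 0.7 the variance is 35%, 25% and 15% lower.

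**The case against.** The strongest reply is that an unadjusted chi-squared test with risk measures is a transparent and acceptable primary analysis for an individually randomised trial. It adds that a condensed article may leave adjusted models to the analysis plan, and that the cost is slight. Most of this stands. The reply fails only in part: the article is not silent but names the final tests, and those tests do not follow its own allocation scheme.

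Several stronger readings are tempting and should not be drawn.

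- A reader might infer that both omissions make the intervals too wide. Only ignoring professional does so, and the widening was seen under the null. In the second model under 5% v 10%, the ratio of mean crude to empirical standard error was about 0.98. If the effect varied between professionals, the crude standard error could even be too small for inference beyond these 48.
- A reader might call the baseline variables strong predictors. The article lists them without prognostic strength.
- A reader might take the fall in crude power from 83.6% to 72.6% as the price of the crude test. Most of it arises because a constant odds ratio shrinks the marginal intervention rate, to about 9.6% at ICC 0.05 and 9.2% at 0.10. Only the difference within each row is attributable.
- The higher ICCs are demanding. At 0.05 the spread between professionals is as large as the mean rate, while the article plans training and a common written document to keep delivery uniform.
- The normality switch cannot touch the binary primary outcome.

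**Conclusion.** The mismatch is real and its direction is clear; its size is uncertain and probably small. On the primary outcome the crude test gives up about 0 to 2 points of power for an ICC of 0.01 to 0.05 and about 4 points at 0.10, with full blocks. Omitted baseline variables cost from nothing to about 2.5 points for R² up to about 0.06. All of these ICC and R² values are assumed. Under the null the crude test errs towards caution, so it carries no excess false-positive risk and a crude result would not be invalid. The case for acting is that the improvement is free and the margin thin: with losses counted as smokers, crude power is already just under the planned 80%. The likely proportional gain is larger for cigarette consumption, a secondary outcome.

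**What to change.** - **Primary outcome:** make the primary test Cochran-Mantel-Haenszel stratified by professional, reporting the Mantel-Haenszel relative risk and risk difference. Optionally add a supportive logistic model with a professional effect, baseline phase and dependence score, named in advance.
- **Cigarettes per day:** use analysis of covariance on the baseline count with professional as a factor, in place of the t test and its normality-triggered switch.
- **Crude chi-squared test:** keep it as supportive.
- **Allocation text:** state that each professional's envelopes form one block, if that is what is meant.

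The cost is wording. The baseline variables are already collected and the professional can be identified from the envelope set; no extra subjects or visits are needed. If many professionals recruit well short of 20, expect little or no gain from stratifying at low ICCs, so the choice should be fixed before outcome data are seen.

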### Ethical approval

This study protocol was approved by the Mallorca Primary Care Research Committee and Balearic Islands Clinical Research Ethics Committee (IB 985/08 PI).

The healthcare professionals participating in the study will sign a document guaranteeing confidentiality of the data. Before initiating the study, the patients must sign an informed consent, which will be obtained following the recommendations in the Declaration of Helsinki.

The Investigator will ensure that this study is conducted in accordance with the principles of the Declaration of Helsinki, ICH Guidelines for Good Clinical Practice and in full conformity with relevant regulations.

All substantial amendments to the original approved documents will be also sent to an appropriate Ethics Committee and Regulatory Authority for written approval.

The trial staff will ensure that the participants’ anonymity is maintained. All documents will be stored securely and only accessible to trial staff and authorised personnel. The study will comply with the Data Protection Legislation which requires data to be anonymised.

## Discussion

Smoking behaviour is one of the major public health problems. As such, all interventions that can be done to protect health and motivate smoking cessation are welcomed, especially if they are simple, non-aggressive, accessible and feasible [23]. If this intervention is performed in primary care, where 90% of the population come over 5 years, the population effect is highly relevant and of great benefit to Public Health.

Although our intervention is addressed to all current smokers, it has been specially designed for those smokers who, due to their great physical and psychological dependence and their balance between positive and negative smoking cessation factors, opt in favour of smoking maintenance. These smokers require forceful information directly related to the effects on their health to change the balance of these factors and allow an opportunity for smoking cessation to take place.

One of the limitations of studies evaluating personal risk relates to those cases in which the results generated by the technology used are normal and, in consequence, reinforce the smoker’s perception about the harmless effects of smoking. We think that the brief advice can minimize this.

The urine cotinine test could be perceived by patients as another intervention for smoking cessation and, therefore, have an effect on smoking cessation. We consider that carrying out the test on both groups minimises this effect.
